## Abstract

**Background:**

Patients with hazardous alcohol intake are overrepresented in emergency departments and surgical wards. These patients have an increased risk of postoperative complications with prolonged hospital stays and admissions to intensive care unit after surgery. In elective surgery, preoperative alcohol cessation interventions can reduce postoperative complications, but no studies have investigated the effect of alcohol cessation intervention at the time of acute fracture surgery. This protocol describes a randomised clinical trial that aims to evaluate the effect of a new gold standard programme for alcohol cessation intervention in the perioperative period regarding postoperative complications, alcohol intake and cost-effectiveness.

**Methods/Design:**

Patients with hazardous alcohol intake undergoing ankle fracture surgery will be recruited into the trial from multiple orthopaedic wards at university hospitals in Denmark, Sweden and Norway. Included patients will be randomly allocated to either standard care or the gold standard programme aimed at complete alcohol abstinence before, during and 6 weeks after surgery. It includes a structured patient education programme and weekly interventions meetings at the orthopaedic outpatient clinic. Furthermore, patients are provided with thiamine and B-vitamins, alcohol withdrawal prophylaxis and treatment, and disulfiram to support abstinence. Alcohol intake is biochemically validated (blood, urine and breath tests) at the weekly intervention meetings and follow-up visits. Follow-up assessments will be conducted 6 weeks and 3, 6, 9 and 12 months after surgery for all patients. The effect of the gold standard programme will be assessed comparing the outcome measures between the intervention and control group at each follow-up point.

**Discussion:**

The study will provide new knowledge about how to prevent alcohol-related postoperative complications at the time of acute fracture surgery. If effective, the results will be a benefit for the clinical course, patients and society alike.

**Trial registration:**

The protocol is registered in ClinicalTrials.gov (Id: NCT00986791).

## Background

Alcohol intake is an independent risk factor for postoperative complications after major and minor operations, elective and emergency procedures for men and women [1]. Patients with hazardous alcohol intake are therefore at increased risk of general infections, wound and pulmonary complications, prolonged hospital stay and admission to the intensive care unit after surgery compared to abstainers or non-hazardous drinkers [2].

The poor surgical outcome is seen in patients with hazardous alcohol intake – even without liver disease, pancreatitis or other alcohol-related diseases [3]*.* The responsible pathophysiological mechanisms include a variety of subclinical dys-functioning organ systems, such as sub-clinical cardiac dysfunction, prolonged bleeding time and en extreme endocrine stress-response to the surgical intervention per se [1,4,5].

The postoperative complication rate is about doubled at an intake as low as > 2 drinks per day [6,7]. However, most of these patients do not have diagnoses commonly associated with alcohol misuse [8]. As all forms of excessive drinking increases the risk of trauma and hospitalisation, hazardous drinkers are overrepresented in emergency departments (ED) and surgical wards [7,9].

Surgical patients as well as patient with trauma seem very motivated to change their lifestyle including drinking habits [10-12]*.* Reviews found that at least two in three of these patients accept alcohol screening and two in three accept participation in alcohol interventions [13]*.* This period has been described as a ‘window of opportunity’, even though it may be very short. Furthermore, one in three reduces their alcohol intake spontaneously, when admitted to surgical wards [14].

Only three alcohol intervention studies have evaluated the effect on postoperative complications in high quality designs. Two randomised clinical trials (RCT) evaluated 4 and 8 weeks of preoperative intensive alcohol cessation intervention for patients drinking 60 g of ethanol per day or more aimed at reduction of postoperative complications. The intervention programme in both RCTs included empowerment to support complete alcohol abstinence, information, weekly visits, and prophylaxis of withdrawal symptoms and relapse with benzodiazepine and disulfiram (DIS) [15]. The compliance was very high, and a recent meta-analysis showed a significant effect on risk reduction and alcohol intake [16]. In contrast, a controlled clinical trial in general elective surgery could not show an effect of brief intervention (BI) aiming at alcohol reduction on postoperative complications [17]. BI consisting of feedback, information and advice have shown low or no effect on alcohol intake over time in general hospital settings and general practice [18-21]. Thus, the effect of BI on alcohol intake seems too small to have an effect on postoperative complications.

A review of cost-effectiveness and cost-benefit studies on screening and BI supported the use of alcohol screening and BI, though the effect was only minor [22]. In trauma patients screening and BI for alcohol problems are cost-effective regarding number of re-trauma [23].

No previous studies have investigated the effect on complications and costs of intensive alcohol cessation intervention at the time of acute surgery. A comprehensive 6-weeks gold standard programme for alcohol cessation intervention (GSP-A) was translated from the previous preoperative alcohol cessation studies as well as studies using the gold standard programme (GSP) [24] for smoking cessation intervention in surgical settings [25]. The GSP-A is also based on evidence from systematic reviews, results from a cross-sectional study on risk factors in a hospital population and patient preferences regarding alcohol intervention in relation to surgery [13,16,26-30].

The aim of this study is to evaluate the effect of the GSP-A aimed at 6 weeks complete alcohol abstinence in the perioperative period for hazardous drinking patients undergoing ankle fracture surgery regarding postoperative complications, alcohol intake and cost-effectiveness up to 12 months after surgery.

## Methods/Design

### Study design and setting

A randomised clinical multi-centre study will be conducted including adult (minimum 18 years) patients undergoing ankle fracture surgery and drinking 21 or more drinks (one drink equals 12 g ethanol) per week for at least 3 months before admission. Patients are consecutively recruited from multiple orthopaedic wards at university hospitals. The centres initially participating in the study are Bispebjerg/Frederiksberg, Hvidovre and Southern Jutland from Denmark, Lund from Sweden as well as Haukeland and Stavager from Norway.

Included patients will be randomly allocated to either the intervention group or control group (standard care). Patients in the intervention group will receive the GSP-A aimed at alcohol abstinence at the time of ankle fracture surgery and 6 weeks after. It includes a structured patient education programme and weekly interventions meetings initially at the orthopaedic ward and continued after discharge at the outpatient clinic (5 in total). Patients in the control group will receive standard care for patients with hazardous alcohol intake according to the clinical guidelines in the wards.

For both groups follow-up assessments will be conducted after 6 weeks and 3, 6, 9 and 12 months after surgery; see trial profile in Figure 1. The primary outcomes are postoperative complications requiring treatment, alcohol intake (abstinence and non-hazardous drinking) as well as cost-effectiveness. The effect of the GSP-A will be assessed comparing the outcome measures between the intervention and control group at each follow-up point.

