### Measures

The primary and secondary outcomes will be evaluated at follow-up points after 6 weeks, 3, 6, 9 and 12 months.

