### Sample size

Sample size calculations are restricted by this being the first study evaluating the effect of alcohol cessation intervention in acute fracture surgery, and the number of patients needed differ depending on the outcome.

The effect on alcohol abstinence is based on the preoperative intensive alcohol interventions, which showed a very high effect above 90% in the intervention groups versus less than 10% in the control groups [16]. However, a more moderate effect is expected in acute fracture surgery with 50% abstainers in the GSP-A group after 6 weeks. This corresponds to a minimum of 2×12 patients.

Postoperative complication rates among ankle fracture patients were 30% for patients drinking at least 5 drinks per day versus 10% in patients without hazardous alcohol intake in a case-control study [42]. If similar complication rates after 6 weeks are expected in the control and GSP-A group respectively, a total maximum of 2×59 patients should be recruited over the 3 to 4 years inclusion period.

The number of patients for the cost-effectiveness analyses is based on the expected effect on the clinical outcomes [43].

All sample size calculations are based on a power of 80% and a risk of type 1 failure on 5%. Also to reduce differences between patient populations, each centre should include about 20 patients.

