### Statistical analyses

The analyses will be performed blinded. The groups are compared regarding primary and secondary outcomes using Chi-square/Fisher’s exact test for frequencies and Mann-Whitney test for continuous outcomes. Analyses will be conducted using intention-to-treat principles. A p-value < 0.05 is considered statistically significant. Subgroup analyses for determination of prognostic factors are done through logistic regression analyses.

The cost-effectiveness of the GSP-A will be estimated by comparing the incremental cost to the incremental effect of the two groups. The GSP-A is considered more cost-effective than standard care if it is less costly and more effective. If the GSP-A is more costly and more effective, the additional cost per abstainer has to be considered worth paying [44].

Data will be analysed using IBM SPSS v. 19 and Excel 2010.

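### Co-equal primary outcomes are each tested at five visits at p<0.05 with none named as decisive, so a false primary claim is well over 5% likely

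*Protocol article*

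**What the plan says.** Under Study design and setting, the protocol article states: "The primary outcomes are postoperative complications requiring treatment, alcohol intake (abstinence and non-hazardous drinking) as well as cost-effectiveness". The list under Primary outcomes repeats these with no ranking.

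Under Measures it adds: "The primary and secondary outcomes will be evaluated at follow-up points after 6 weeks, 3, 6, 9 and 12 months". Study design and setting makes each visit an occasion for comparing the groups: "The effect of the GSP-A will be assessed comparing the outcome measures between the intervention and control group at each follow-up point".

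Statistical analyses names the tests ("The groups are compared regarding primary and secondary outcomes using Chi-square/Fisher’s exact test for frequencies and Mann-Whitney test for continuous outcomes") and one threshold for all of them: "A p-value < 0.05 is considered statistically significant". Cost-effectiveness has its own paragraph and criterion there: "The cost-effectiveness of the GSP-A will be estimated by comparing the incremental cost to the incremental effect of the two groups". That paragraph gives no p-value.

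Sample size treats abstinence (2×12) and complications (2×59) separately. Both use rates after 6 weeks, and "All sample size calculations are based on a power of 80% and a risk of type 1 failure on 5"%. The section does not call 6 weeks the primary time point, and the stated aim in Background runs up to 12 months.

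**The concern.** With several primary outcomes, several visits and one flat threshold, the plan does not say which result would count as showing that the programme works. A reader could take a single significant comparison, on any primary outcome at any visit, as a positive trial. If the programme had no effect, such a result would turn up far more often than 5% of the time.

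The stake is concrete because the two clinical outcomes differ greatly in how easily they can be shown: by the plan's own figures, abstinence needs 12 per group and complications 59. The Discussion wants the trial to inform guidelines for perioperative care, so it matters whether a positive claim rests on complications, on drinking, or on one visit among five.

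The missing SAP does not remove the point. The protocol itself fixes the primary outcomes, the visits, the tests and the threshold, and the problem comes from that combination.

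**Working it through.** **1. The plan's own sample sizes.** Inputs from Sample size: complications 30% v 10% (the rates seen in heavier and in non-hazardous drinkers in an earlier case-control study, applied here to the control and programme groups), 80% power and 5% type 1 risk. Sidedness is not stated; two-sided is assumed. With the unpooled two-proportion formula:

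n = (1.960 + 0.842)² × (0.3×0.7 + 0.1×0.9) / 0.2² = 7.849 × 0.30 / 0.04 = 58.9, so 59 per group. The stated 2×59 is reproduced.

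For abstinence, the same formula at 50% v an assumed 5% (the plan says only less than 10% for controls) gives 7.849 × (0.25 + 0.0475) / 0.45² = 11.5, so 12 per group. The stated 2×12 is reproduced on that assumption; at 50% v 10% the formula gives 17.

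Both sizes therefore fit a full, unadjusted two-sided 5% for one outcome at one visit. No allowance for several tests is built in.

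**2. Counting the tested primary comparisons.** Complications plus one alcohol outcome is 2 outcomes; with abstinence and non-hazardous drinking counted separately it is 3. Over five visits this is 2×5 = 10 or 3×5 = 15. Cost-effectiveness is left out because its stated criterion has no p-value.

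**3. Upper reference, independent tests:** 1 − 0.95^k.

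- k = 10: 40.1%
- k = 15: 53.7%
- 6 weeks only: k = 2, 9.8%; k = 3, 14.3%

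**4. Correlated tests.** The documents give no correlations, so these are assumptions: 0.7 to 0.9 between visits within an outcome, and 0 to 0.6 between outcomes. Simulating jointly normal test statistics under no effect (400,000 runs), and counting runs in which any |z| exceeds 1.96, gives:

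| Tests | Lowest | Highest |
|---|---|---|
| 2 outcomes × 5 visits | 17.2% | 27.5% |
| 3 outcomes × 5 visits | 22.6% | 38.2% |
| 2 outcomes, 6 weeks only | 8.8% | 9.8% |
| 3 outcomes, 6 weeks only | 11.8% | 14.3% |

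Even one outcome over five visits gives about 10% to 15%.

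**5. A more literal model.** Take 59 per group, with abstinence nested over time (falling from 30% to 15%) and complications cumulative (rising from 20% to 30%). These rates are assumed, equal in both groups, and the two outcomes are independent. The chance of at least one significant result among the 10 tests is about 22% with uncorrected chi-square and 13% with Fisher's exact test.

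**6. Cost of two remedies.** Bonferroni with the formula in step 1 would need 72 per group for 2 tests (power at 59: 71%) and 79 for 3 tests (66%). A fixed sequence keeps 5% for each step, so 2×59 stands for whichever outcome is tested first. Power of that first test at 59 per group, two-sided 5%:

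- abstinence 50% v 10%: 99.9%
- abstinence 50% v 20%: 94%
- abstinence 40% v 20%: 67%
- complications 30% v 10%: about 80%

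For abstinence, only the 50% in the programme group is the plan's figure; the other rates are assumptions.

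**The case against.** A reader might infer that the 5% type 1 risk in Sample size is not kept. The document does not support that. The 5% is an input to each separate calculation, each single test does hold it, and no 5% across all primary claims is promised. What is missing is a rule for the set.

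A reader might also count four primary outcomes at five visits, giving 20 tests. Statistical analyses does not support this, because cost-effectiveness is judged by incremental cost against incremental effect with no p-value.

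The tests are also far from independent. Abstinence is specified as continuous and is nested within non-hazardous drinking, and complications may be counted cumulatively. The 40% to 54% figures are therefore upper references only, and Fisher's exact test, which the plan also names, would lower the risk further. This stands, yet the lowest figure found over all visits is still about 13%.

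The strongest counter-argument is that both sample sizes rest on 6-week rates, so 6 weeks is the implied primary visit. That is a reasonable guess, but the protocol never says so and elsewhere treats all five visits alike. Even if it is granted, two or three co-equal tests remain. Had success required all primary outcomes to be significant, there would be no inflation, but no such rule is stated.

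Finally, a detailed multiplicity procedure is often left to an SAP. That is fair for the mechanics. It does not cover a protocol that itself puts the outcomes, visits and threshold on an equal footing.

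**Conclusion.** The point holds for what the protocol itself fixes: unranked primary outcomes, a comparison at each of five visits, p<0.05 throughout, and no decisive outcome, visit or success rule. The tested primary family is 10 to 15 comparisons. The chance of at least one false-positive primary result is about 17% to 38% under the assumed correlations, and up to about 10% to 14% if only 6 weeks counts. The size depends on those correlations and on the test used; the direction does not, since every scenario examined with more than one test exceeds 5%.

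Nothing in the document shows an intention to select favourable results. The finding is that the plan as written would not prevent it.

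**What to change.** Before the group code is broken, add to Statistical analyses:

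- The decisive visit is 6 weeks, the point used in Sample size.
- Complications and biochemically validated abstinence at 6 weeks are tested in a fixed sequence, each at two-sided 5%; the second is claimed only if the first is significant. The sponsor chooses and states the order. Complications first follows the document's own listing; abstinence first is an alternative.
- Non-hazardous drinking and all 3- to 12-month comparisons are supportive and are reported as estimates with 95% confidence intervals.
- Cost-effectiveness remains an incremental cost and effect estimate outside the tested family.

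This needs wording only and no more patients, but it has a price. Later visits lose confirmatory status although the aim runs to 12 months, and the second outcome depends on the first. With complications first, the gate passes about 80% of the time under the plan's rates. With abstinence first it is nearly certain to pass at 50% v 10%, but not at 40% v 20% (67%).

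Project status says inclusion ended in 2014 and short-term analysis is ongoing. The analyses are described as blinded, but the document does not show whether the code is still unbroken. The report should therefore state when the order was fixed relative to unblinding.

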**Figure 1 Fig1:**
[figure not shown]
Trial profile.

### Recruitment process and inclusion criteria

All ankle fracture patients admitted to the orthopaedic wards and scheduled for surgery are screened for eligibility by the research staff, and patients fulfilling the inclusion, but not the exclusion criteria, are invited to participate in the trial. The inclusion criteria are traumatic ankle fracture requiring internal fixation (osteosynthesis), informed consent, and randomisation within 36 hours after entering the orthopaedic ward. The fracture can be open or closed as well as simple or comminuted. The exclusion criteria are major trauma involving other fractures or major lesions, preoperative severe psychiatric disorders (including drug addiction, severe alcohol dependence [defined as experience of delirium or seizures during abstinence from alcohol] and dementia) or other conditions of reduced ability for giving informed consent; pathological fractures, pregnancy and lactation; allergy to benzodiazepines or DIS; uncompensated chronic diseases (including fulminant cardiac or liver insufficiency, which are contraindications for DIS) or ASA score 4-5 [31]; cancelled operation and withdrawal of informed consent.

Patients are included after informed consent, which can be obtained before or after the operation but within the 36 hours after admission. The patients can withdraw the informed consent at any time without any explanation and without consequences for their treatment or contact to the staff. For patients not giving or withdrawing their informed consent research staff will ask permission for follow-up via their medical recording solely for the purpose of the project.

### Randomisation, allocation concealment and sequence generation

A computer-generated list of random numbers will be used for allocation of the patients. The randomisation sequence is created using www.sealedenvelope.com statistical software, and is stratified by centre with a 1:1 allocation using random block sizes. The list is generated by a researcher not otherwise involved in the project and prior to the commencement of recruitment. The allocation sequence will be concealed from the research staff enrolling and assessing participants in sequentially numbered, opaque, sealed and stapled envelops that are impermeable to intense light. Corresponding envelops will be opened only after the patients have given informed consent and it is time to allocate the intervention group.

### Data collection

Baseline data will be collected for all included patients during admission in interviews: A detailed alcohol profile on intake over time (Timeline Follow-back [32]), ICD-10 criteria for alcohol dependency [33], test for alcohol use disorders (AUDIT-C [34]), alcohol withdrawal symptoms (CIWA-Ar [35]), breath test (ethanol during expiration), blood sampling for liver function (haemoglobin, alkaline phosphates, gamma-glyteryl-transferase, amino-transferases, bilirubine) and for alcohol markers (carbohydrate-deficient transferring, ethanol, phosphatidylethanol, mean cell volume, serum, EDTA–plasma and citrate-plasma); urine sampling for alcohol markers (ethyl glucuronide, ethyl sulphate, ethanol).

Furthermore, baseline characteristics regarding age and sex, socio-demographic factors, other lifestyle factors (smoking, overweight, risk of malnutrition and physical inactivity [36]), co-morbidity, self-rated ankle function, and self-evaluated health assessed in the SF-36 questionnaire [37] will be obtained for all patients.

During admission the following information will be collected from the medical records: AO-classification of the ankle fracture and surgical characteristics; ASA-score [31], operative procedure, antibiotics and thrombo-embolic prophylaxis, type of anaesthesia, blood loss, infusions, implants and surgical or anaesthetic problems. Besides, length of hospital stay, use of resources and medicines, discharge or transfer will be registered for all patients.

Follow-up visits will be conducted after 6 weeks, 3, 6, 9 and 12 months in the orthopaedic outpatient clinics. Patients will be evaluated on postoperative complications and second surgery, Olerud-Molander Ankle Score [38], dorsal plantar flexibility (after 3, 6, 9 and 12 months) and fracture status after 12 months confirmed by x-ray (satisfactory healing, secondary dislocation or non-union. Effect on alcohol intake will be assessed by Timeline Follow-back [32], alcohol withdrawal symptoms (CIWA-Ar [35]), breath test (ethanol during expiration) as well as blood sampling for liver function, alcohol markers and urine sampling for alcohol markers. Besides data on rehabilitation, readmissions, ED, general practitioners, specialist doctor, physiotherapist and occupational therapist, alcohol treatment services, nursing home, community nurse, home care, return to work and/or previous activity level, and use of medicines will be collected at all follow-up points.

All personal research data will be handled confidentially and anonymously after collection in the case report files. Only the study identification number and no personal identification data will be entered in the research database.

